Interprofessional teams consisting of registered nurses, physiotherapists, and occupational therapists will be involved in this study. They will perform 2 health needs assessments of home-living older adults, initially at baseline and then after a period of 5 months. These assessments cover several factors, including physical (mobility and sensory), cognitive, psychological (depression), social (loneliness), and behavioral (alcohol consumption). The objectives of our study are 3-fold: first, to assess changes in frailty levels in home-living older adults over 5 months; second, to explore the observable functional changes from a prestudy baseline (t1) to a poststudy period (t2) and how these changes correlate to frailty levels; and finally, to gain deeper insight into the perspectives of older adults and their informal caregivers to enhance the feasibility of implementing this type of health needs assessment within municipal health and care services.

The research questions that guide the study are (1) What observable changes, if any, can be identified in the frailty levels of home-living older adults over a period of 5 months? (2) Are there identifiable changes in functions that can be observed from t1 to t2, and how these changes relate to frailty levels? and (3) What are the perceptions of home-living older adults regarding the feasibility of the health needs assessment, with regard to its content, delivery, and procedures?

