## Methods

### Study Design

This pre-post study, registered on ClinicalTrials.gov (NCT05837728), is based on a case-only design to conduct health needs assessments, initially at the baseline and then after 5 months. The study is conducted as part of the research project “More good days at home: Advancing health-promoting practices in municipal health care services for older recipients of home care,” funded by the Norwegian Research Council (320622).

To gain in-depth insights, we use a 2-step research process. In the first step, a quantitative approach will be applied to examine changes in frailty levels in home-living older adults over 5 months. In addition, we will examine observable functional changes from t1 to t2 and how these changes correlate to frailty levels.

Following this, a qualitative approach will be used to investigate the perspectives of participants and their informal caregivers concerning the health needs assessment and its acceptability.

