### Recruitment

Participant recruitment was conducted in collaboration with 3 health and welfare service departments in a municipality in the western region of Norway between February 1 and June 26, 2023. Health care professionals purposively selected participants according to the eligibility criteria. During their initial phone contact with potential participants, health care professionals used their professional judgment to assess the individual’s ability to understand the research project and provide informed consent to participate.

Subsequently, health care professionals asked a designated research team member, a nurse with experience in mental health, to obtain informed consent from those who meet the initial criteria. To ensure consistency in the process, the same nurse visited all potential participants for the consent process. Potential participants were then given time to consider this information before giving their written consent.

The design of our health needs assessment package includes a cognitive assessment. This approach ensures that participants identified with cognitive impairment in the first assessment are not included in the second assessment.

We aim to enroll 40 participants in the quantitative phase of this study, in line with the agreement made with the municipality at the beginning of the project, taking into account their resource limitations. In the next phase, which uses a qualitative approach, we plan to invite all 40 participants for an interview, with the actual number of interviews conducted depending on the participants’ consent to participate. To capture diverse perspectives, we will strive to include a group of home-living older adults who differ in terms of age, gender, marital status, living situations, and health care needs.

The aforementioned sample size takes into account the limited resources available for the project, including budget constraints, personnel resources, and time limitations, while ensuring the collection of meaningful data to address the research questions.

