### Outcome Measures

This study has two primary outcome measures: (1) identifying changes in frailty levels of home-living older adults over a period of 5 months and (2) assessing any observed changes in functions from t1 to t2 and how these changes relate to the level of frailty.

In addition to the primary outcome measures, this study will also evaluate the feasibility of the health needs assessment. Emphasis will be placed on the acceptability of the assessment among older adults and their informal caregivers, as well as the practicality of implementation in relation to time and resource constraints.

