### Data Analysis

#### Quantitative Analyses

The statistical package SPSS (version 29; IBM Corp) will be used for all statistical analyses. Descriptive statistics will be used to provide an overview of the demographic variables. Given the exploratory nature of this study and the limited sample size, our analysis involves looking at the data from multiple perspectives. The aim is to uncover patterns and relationships that could inform the development of hypotheses for future studies.

To answer the research questions, we will first calculate descriptive statistics for changes in frailty levels between 2 time points, using mean and SD or median and IQR for a skewed distribution. This will be followed by paired comparisons using either 2-tailed *t* test or the Wilcoxon test. We will also examine the association between the changes in frailty and baseline levels by plotting and estimating correlation coefficients (Pearson and Spearman). We will further assess changes in functional variables and the bivariate associations between these changes and the change in frailty.

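### Primary outcome 2 asks how functional change relates to the level of frailty, but the planned analysis relates it only to the change in frailty

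*Protocol article*

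**What the plan says.** Five statements of the second aim refer to frailty as a level.

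- Outcome Measures, primary outcome 2: "assessing any observed changes in functions from t1 to t2 and how these changes relate to the level of frailty".
- Introduction, research question 2: "Are there identifiable changes in functions that can be observed from t1 to t2, and how these changes relate to frailty levels".
- Study Design: "we will examine observable functional changes from t1 to t2 and how these changes correlate to frailty levels".
- The Methods part of the abstract and the objectives in the Introduction say the same in nearly the same words.

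The Quantitative Analyses section, which sets out how the research questions will be answered, gives two analyses that bear on this.

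- For function: "We will further assess changes in functional variables and the bivariate associations between these changes and the change in frailty".
- For frailty: "We will also examine the association between the changes in frailty and baseline levels by plotting and estimating correlation coefficients (Pearson and Spearman"). This is the only planned analysis that mentions a level, and it pairs that level with change in frailty, not with functional change.

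The section describes the work as exploratory: "Given the exploratory nature of this study and the limited sample size, our analysis involves looking at the data from multiple perspectives". The sample size of 40 was set by agreement with the municipality and by resources. No power target is stated.

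**The concern.** Whether people at a higher frailty level change more in function is one question. Whether people whose frailty shifts also shift in function is another. The outcome and research question, read literally, ask the first; the analysis section answers the second.

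The association half of one of only two primary outcomes therefore has no analysis that matches its wording. If the change-with-change correlation is reported under the outcome as worded, readers will take it as a statement about frailty level. The study is meant to generate hypotheses for later work, so a mislabelled association would carry the wrong hypothesis forward. If the mismatch stays open, the choice between level and change could also be made after both results have been seen.

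**Working it through.** The article gives no figure to reproduce here. The check has three parts: comparing the texts, asking whether one association can stand in for the other, and asking whether the other planned correlation fills the gap.

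**1. Side by side**

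| Place | Functional side | Frailty side |
|---|---|---|
| Abstract (Methods), Introduction, Study Design, Outcome Measures | change, t1 to t2 | level; visit not named |
| Quantitative Analyses, functional association | change, t1 to t2 | change |
| Quantitative Analyses, baseline-level association | not a functional change | change in frailty, against baseline levels |

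No row of the analysis section pairs functional change with a frailty level.

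**2. Can the change association stand in for the level association?**

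Let dX be functional change, F1 and F2 the frailty scores at t1 and t2, a = corr(dX, F1), b = corr(dX, F2) and rho = corr(F1, F2). If F1 and F2 have equal SDs, then

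corr(dX, F2 - F1) = (b - a) / sqrt(2(1 - rho)).

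The article gives no rho, so I assume 0.6, 0.8 and 0.9. The denominators are sqrt(0.8) = 0.894, sqrt(0.4) = 0.632 and sqrt(0.2) = 0.447. The values of a and b are illustrative, and every combination below gives a valid (positive definite) correlation matrix.

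| a (with t1 level) | b (with t2 level) | b - a | rho 0.6 | rho 0.8 | rho 0.9 |
|---|---|---|---|---|---|
| 0.30 | 0.30 | 0 | 0.00 | 0.00 | 0.00 |
| 0.30 | 0.10 | -0.20 | -0.22 | -0.32 | -0.45 |
| 0 | 0.20 | 0.20 | 0.22 | 0.32 | 0.45 |

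- Row 1: a real relation with level at both visits, and none with change.
- Row 2: positive relations with level, and a negative one with change.
- Row 3: no relation with baseline level, and a positive one with change.

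**3. Does the other planned correlation close the gap?**

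Take the baseline levels to be baseline frailty. The plan then yields corr(dX, dF) and corr(dF, F1), where dF = F2 - F1. Under equal SDs, corr(dF, F1) = -sqrt((1 - rho)/2), which is -sqrt(0.1) = -0.316 at rho = 0.8. Given two of three correlations, p and q, the third can lie anywhere in pq ± sqrt((1 - p²)(1 - q²)). With p = 0 and q = -0.316 that is 0 ± sqrt(0.9), or -0.95 to 0.95. The two planned results together say almost nothing about corr(dX, F1). If the baseline levels are functional ones, the analysis contains no frailty level at all.

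**The case against.** The best reply is that frailty level is used loosely for the score itself. Outcome 1 concerns changes in frailty levels, the analysis section shortens that phrase to change in frailty, and the Discussion speaks of the dynamics and progression of frailty. On that reading the authors planned the analysis they meant and worded the outcome loosely. This may well be so, and the text does not settle it. But the Outcome Measures section uses changes in levels for outcome 1 and level for outcome 2 in the same sentence, and the analysis section separates change from baseline level. On the loose reading, the wording of the outcome still has to be corrected.

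The reply can add that the study is openly exploratory and that its limitations section claims only possible correlations and patterns. That stands and limits the harm. The promise of several perspectives, however, names no further analysis. Nor is this a detail left to a fuller document: the article does state the analysis, and it names a different quantity from the outcome.

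A reader might infer two stronger points, and the documents support neither.

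- That primary outcome 2 is not analysed at all. It has two parts, and the first, change in function from t1 to t2, is explicitly planned.
- That the change-with-change correlation is the statistically weaker choice. The article gives no reliability, spread of CFS change or expected correlation from which to judge this. Unreliable functional change scores would weaken either analysis.

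**Conclusion.** The point holds for the association half of primary outcome 2 and research question 2. They ask about frailty level, the plan analyses change in frailty, and a result for one cannot be reported as a result for the other. In the illustrations, a correlation of 0.30 with level at both visits becomes 0 with change, and 0.30 falling to 0.10 becomes -0.22 to -0.45.

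These figures rest on equal frailty SDs at the two visits, an assumed rho of 0.6 to 0.9 and Pearson correlations. With unequal SDs or ranks the exact values would move, but the two quantities would remain distinct. The mismatch in wording needs none of these assumptions.

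The severity is moderate. A primary outcome is affected, but the study is exploratory, no sample size or confirmatory test depends on this correlation, and the authors may simply have meant change in frailty.

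**What to change.** Decide which quantity is meant before the t2 data are analysed, and make the sections agree.

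- **If level is meant:** in Quantitative Analyses, add for each functional variable the association of its t1-to-t2 change with the CFS level at a stated visit, with an estimate, 95% CI and plot. The t1 level is a natural choice, but the outcome names no visit, so the authors must say. Keep the change-with-change association under its own label.
- **If change is meant:** reword the outcome, research question 2, the objective, the design section and the abstract to change in frailty, and leave the analysis as it is.

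Neither route needs new measurements, because the CFS and the functional measures are planned at both visits. The Results section reports the second assessments as still ongoing, so the choice can be fixed before the results are seen. The first route costs one more set of exploratory correlations in at most 40 people; the second costs wording only.

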#### Qualitative Analyses

The interview transcripts will be read thoroughly and reread to ensure familiarity with the content. NVivo (version 12; Lumivero) software will be used to help organize and code the data. The data analysis will be carried out using a thematic analytical approach based on the guidelines of Braun and Clarke [70].

### Patient and Public Involvement

In this study, older adult participants were not involved in developing the study design or objectives. The study design and objectives were developed by the researchers of this study in collaboration with the local municipality stakeholders. The Service User Association for Older Adults in Norway (*Pensjonistforbundet*) contributed insights to the grant application, which was successfully funded by the Research Council of Norway. Furthermore, details about the study design and recruitment procedures were provided to health care professionals prior to data collection.

### Ethical Considerations

Ethics approval was obtained from the Regional Committees for Medicine and Health Research Ethics (REK) of West Norway on November 15, 2022 (523455). The project was subsequently approved by the Norwegian Agency for Shared Services in Education and Research (SIKT) on January 19, 2023 (100847), which ensures that adequate safeguards are in place to protect the privacy of participants and to maintain the confidentiality of data. This study will be conducted in accordance with the Declaration of Helsinki guidelines [71] from REK and the Data Protection Impact Assessment (DPIA). It will also be conducted under the principle of informed consent. Prior to data collection, all the participants who agreed to participate in the study will sign a consent form, which includes a description of the study, its objectives, and participants’ involvement and rights. Participation in the study is entirely voluntary and participants can withdraw at any time. Additionally, participants are entitled to access the information documented about them and to make necessary corrections to any errors discovered.

### Data Management

#### Overview

The project manager will supervise the day-to-day operation of the project and be responsible for ensuring that DPIA guidelines are followed.

#### Data Collected From the Frailty Assessment

The collected data will be registered electronically and directly submitted to TSD for secure storage and processing. The code list that links personal identification information to the individual participant will be secured by the project manager to ensure there is no unauthorized access to the information. Only the selected project team members will have access to the anonymized data sets. No other party will have access to the research data prior to dissemination. Furthermore, other paper-based research data will be anonymized and kept in locked cabinets or archives that are only accessible to project team members.

#### Data Collected From the Interview

Only a designated member of the research project and the project manager will have access to the audio files stored at Nettskjema. The interview will be transcribed into written text and all personal identifiers will be removed to ensure anonymity. The transcription will be shared with other project team members as appropriate. This data will be retained until December 31, 2026, and then deleted from TSD.

## Results

The initial baseline assessments were completed in July 2023, and the second health needs assessments are ongoing. We expect the results to be available for analysis in the spring of 2024.

## Discussion

### Principal Considerations

Studies have documented that frail older adults have an elevated risk of negative health outcomes [13,14]. Early assessment of frailty in older adults is, therefore, crucial, and is recommended. Despite its recognized importance, assessing frailty is not considered a standard clinical practice in many health care systems [18], including in Norway [72]. This situation is understandable as such an assessment often requires significant resources, which many health care facilities lack [73].

Our study is carefully designed to reflect real-world applications and settings, with a particular focus on municipal health care in Norway, where health care professionals tend to have heavy workloads. These conditions pose a challenge to incorporating additional tasks, such as a frailty assessment, into routine health needs assessments. As mentioned earlier, older adults typically turn to their local municipality for home care services and health care professionals make home visits to assess their care needs. This assessment process uses the standardized tool (The Norwegian Information System for the Nursing and Care Sector [*Individbasert pleie- og omsorgsstatistikk*; IPLOS]), which was developed to optimize care needs assessments in Norway [33]. Despite being a standardized tool, IPLOS has been criticized for being too subjective, as assessments appear to vary widely among health care professionals [74].

In response to these challenges, we aim to refine the health needs assessment process to improve objectivity and consistency, and to highlight the critical needs to incorporate frailty assessments into routine municipal care practices. The path begins with selecting appropriate measurement tools that are meaningful and practical, and training interprofessional teams to implement them. Part of this training process includes the task of conducting assessments and discussing the results to make informed decisions.

Beyond integrating assessments, our study aims to shed light on the dynamic nature of frailty and provide a deeper understanding of the factors that impact its progression. This insight could potentially help older adults and their informal caregivers to manage frailty. Additionally, it can better prepare health care professionals to develop and implement strategies aimed at delaying and mitigating the progression of frailty.

### Strengths and Limitations

This study has several strengths. First, it deepens our understanding of frailty as a complex condition and highlights how levels of frailty and related functional changes can differ. Moreover, because the study is designed to reflect the real-world settings and applications, it can help improve health care practices in the municipal sector. The involvement of local stakeholders in the municipality from the planning to the implementation phase ensures that the study remains relevant and applicable, thereby facilitating the translation of knowledge into practice. Additionally, the inclusion of home-living older adults’ and their informal caregivers’ perspectives can help facilitate improvement in the feasibility of the assessment.

As with other studies, this study has its limitations, particularly with regard to the relatively small sample size and the absence of a control group. This could lead to misinterpretation of the observed changes, either in the support or services for participants, other confounding factors, or due to a habituation effect over the 5-month period. Consequently, this limitation may also potentially impact the internal validity of the study, as well as the construct validity of the study [75]. To address this challenge, we will carefully compare our findings with those of previous studies investigating similar approaches to aiding the interpretation of outcomes.

Despite its inherent limitations, this study will serve as an important first step in developing a more systematic health needs assessment for home-living older adults and the development of health promotion strategies that can improve these older adults’ quality of life.

Nonetheless, the results should be interpreted with caution due to the absence of a control group, the limited sample size, and the potential underrepresentation of all home-living older adults. These limitations suggest that the results indicate possible correlations and patterns, rather than confirming a definite relationship or establishing specific cause-and-effect relationships.

## Abbreviations

DPIA: Data Protection Impact Assessment
IPLOS: The Norwegian Information System for the Nursing and Care Sector (Individbasert pleie- og omsorgsstatistikk)
REK: Regional Committees for Medicine and Health Research Ethics
SIKT: Shared Services in Education and Research
TFA: Theoretical Framework of Acceptability
TSD: Services for Sensitive Data (Tjenester for Sensitive Data)
